### Dengue outbreak signals

As a complementary approach for evaluating the public health impact of large-scale
*Wolbachia* releases, we will also use the following dengue outbreak alert tools routinely used in public health practice. We hypothesise that these dengue outbreak signals will not be triggered in areas where
*Wolbachia* has been established.

**1. Control diagram (endemic channel)**

The definition of a dengue outbreak or epidemic has changed over time in Brazil. In Rio de Janeiro and Niterói, a control diagram is currently used to monitor dengue incidence. Briefly, the control diagram is constructed from a five-week centered moving average of weekly notified dengue incidence for the past five years excluding epidemic years. An early signal of a dengue outbreak/epidemic is triggered when the weekly incidence of dengue crosses the upper limit of the control diagram
^26^, with the upper limit defined as [mean+(standard deviation*1.96)]. Incidence that remains above the upper limit of the control diagram for two or more consecutive weeks constitutes a dengue outbreak. For the purpose of monitoring the impact of
*Wolbachia* releases on dengue, we will construct annual control diagrams with weekly dengue incidence, by city and for each release and non-release zone, to monitor the occurrence of dengue outbreaks. The number of dengue outbreak signals triggered per year will be reported.

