## Methods

### Study design

The aim of this epidemiological study is to test the hypothesis that the establishment of
*Wolbachia* in local
*Ae. aegypti* populations in Rio de Janeiro and Niterói leads to a reduction in the burden of
*Aedes*-borne disease.

The impact of
*Wolbachia* deployment on disease incidence will be evaluated using routine notifiable disease surveillance data to describe associations between temporal and spatial trends in dengue, chikungunya and Zika and the deployment of
*Wolbachia* across Niterói and Rio de Janeiro, with two objectives:

1. Estimate the reduction in dengue, chikungunya and Zika in the aggregate treated areas of Niterói and Rio de Janeiro compared to an untreated control area, and in each treated zone compared to the untreated control area, each year for five years after
*Wolbachia* establishment.2. Quantify the occurrence of dengue outbreak signals in
*Wolbachia* treated areas compared to untreated areas in Niterói and Rio de Janeiro, for five years after
*Wolbachia* establishment, using outbreak indicators employed routinely for public health monitoring of dengue activity: i) control diagrams comparing the weekly dengue incidence (five-week moving average) against the five-year historical average in that same area; and ii) outbreak incidence threshold of 300/100,000 population in any month.

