**2. Classical incidence threshold**

Another outbreak definition that has been used by the Ministry of Health (MoH) in previous years
^20,
22,
23^ is a dengue incidence threshold of ≥300 cases/100,000 population in a given month. Although not included in current MoH guidelines, this provides an alternative endpoint for evaluating dengue activity at a population level in the post-intervention period, compared with pre-intervention, and we will report the number of months in a given year where dengue incidence crosses this threshold.

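### The control-diagram limit for each zone is drawn from that zone's own past five years with no pre-release anchor, so a lasting effect is increasingly attenuated in the outbreak-signal comparison

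*Protocol article*

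**What the plan says.** Objective 2 in the article's Study design section quantifies dengue outbreak signals in treated compared with untreated areas over five years after establishment. It uses two indicators: a control diagram, and an absolute monthly threshold of 300 per 100,000. The control diagram sets weekly incidence "against the five-year historical average in that same area".

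The section on the control diagram gives the construction: "the control diagram is constructed from a five-week centered moving average of weekly notified dengue incidence for the past five years excluding epidemic years". The upper limit is the mean plus 1.96 standard deviations. "Incidence that remains above the upper limit of the control diagram for two or more consecutive weeks constitutes a dengue outbreak". For monitoring the impact of releases, the authors state that "we will construct annual control diagrams with weekly dengue incidence, by city and for each release and non-release zone", and the yearly number of signals will be reported.

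The opening of the Dengue outbreak signals section calls this a complementary approach and states the expectation: "We hypothesise that these dengue outbreak signals will not be triggered in areas where" *Wolbachia* is established.

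No sentence fixes the reference years before release. The article does not say how an epidemic year is identified, or whether an excluded year is replaced by an earlier one.

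**The concern.** A control diagram asks whether this year is unusual for this place. That suits operational surveillance. It is a poor yardstick for a lasting intervention if the intervention's own years become part of what counts as usual.

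In a treated zone with a sustained reduction, each post-release year that enters the window lowers the limit. The control zone's limit has no such drift. The two zones' signal counts are then measured against yardsticks that move apart, and the contrast shrinks although the true effect is constant. Late in follow-up, treated zones could register signals or outbreaks at low absolute incidence, and this could be misread as waning of the intervention.

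**Working it through.** The article gives no power or expected count for the outbreak signals, so there is no figure to reproduce.

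**Inputs from the article.** Five-year same-area window, annual diagrams, and limit of mean plus 1.96 SD (Study design; Control diagram). Releases complete by the end of 2019 and data to 2023 (Current study status). Outcome report two years after releases end (Dissemination). Relative risks (RR) of 0.6, 0.5, 0.4 and 0.3 (power simulation in the interrupted time series section).

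**Step 1: how many baseline years are post-release.** With a five-calendar-year window, post-years 1, 2, 3, 4, 5 and 6 contain k = 0, 1, 2, 3, 4 and 5 post-release years. By calendar:

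| Last pre-effect year of the zone | k in the 2021 diagram (window 2016–2020) | k in the 2023 diagram (window 2018–2022) |
|---|---|---|
| 2017 | 3 | 5 |
| 2018 | 2 | 4 |
| 2019 | 1 | 3 |

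**Step 2: shift of the baseline mean.** With constant RR, baseline mean ÷ untreated mean = 1 − (k/5)(1 − RR). Treated incidence ÷ own baseline mean is therefore RR / [1 − (k/5)(1 − RR)]. For RR 0.5 and k = 4: 0.5 / (1 − 0.8 × 0.5) = 0.5 / 0.6 = 0.83.

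| RR | k=0 | k=1 | k=2 | k=3 | k=4 | k=5 |
|---|---|---|---|---|---|---|
| 0.6 | 0.60 | 0.65 | 0.71 | 0.79 | 0.88 | 1.00 |
| 0.5 | 0.50 | 0.56 | 0.63 | 0.71 | 0.83 | 1.00 |
| 0.3 | 0.30 | 0.35 | 0.42 | 0.52 | 0.68 | 1.00 |

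At k = 5 both mean and SD are multiplied by RR, so limit(RR·x) = RR·limit(x). If no years are excluded, the chance of a signal then equals that without the intervention. For k between 1 and 4 the SD also contains the step between pre- and post-release years, so the ratio of means alone does not give the signal frequency. Step 3 allows for this.

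**Step 3: signal frequency by simulation.** Assumptions, not from the article: population 200,000, mean 5 per 100,000 per week, seasonal pattern, between-year log-SD 0.6 or 1.0, autocorrelated weekly noise, 800 runs per setting. The five-week average is compared with the limit. The table gives the treated/control ratio of weeks above the limit.

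| Setting | Moving window, post-years 1 to 6 | Fixed pre-release window, years 1 to 6 |
|---|---|---|
| RR 0.5, log-SD 0.6, no exclusion | 0.16, 0.21, 0.28, 0.47, 0.57, 1.03 | 0.12–0.17 |
| RR 0.3, log-SD 0.6, no exclusion | 0.03, 0.04, 0.03, 0.12, 0.31, 1.02 | 0.01–0.05 |
| RR 0.5, log-SD 1.0, no exclusion | 0.34, 0.41, 0.47, 0.59, 0.78, 1.00 | 0.28–0.38 |
| RR 0.5, log-SD 1.0, years above an assumed 500 per 100,000 excluded, not replaced | 0.40, 0.51, 0.51, 0.53, 0.59, 0.63 | 0.42–0.47 |
| RR 0.3, same exclusion | 0.22, 0.24, 0.25, 0.34, 0.41, 0.49 | 0.20–0.24 |

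In the first setting, the probability of at least one outbreak in a treated zone-year goes 0.09, 0.09, 0.12, 0.18, 0.24, 0.32 with the moving window (control 0.30–0.38). With the fixed window it stays at 0.07–0.09 (control 0.30–0.34).

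**Step 4: excluded epidemic years.** Dropping a pre-release year without replacement raises the post-release share. With two post-release years, 2 of 5 becomes 2 of 4, and at RR 0.5 the ratio moves from 0.63 to 0.5 / (1 − 0.5 × 0.5) = 0.67. An absolute cut-off works the other way in the simulation: erosion is slower and incomplete at year 6. The text does not determine which applies.

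**The case against.** The strongest reply is that a moving window is an inference. The sentence on the past five years describes the health departments' existing tool, the sentence on what the study will do names no reference years, and objective 2 speaks of a historical average, a word the article uses elsewhere for the pre-intervention period. A fixed pre-release reference is therefore possible. It is the weaker reading: the construction is taken over expressly to monitor the impact of releases, the diagrams are annual, and nothing anchors them.

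A second reply concerns timing, and it stands. The outcome report is planned for two years after releases end. In the 2021 diagram a zone whose last pre-effect year is 2019 has one post-release baseline year, and at RR 0.5 the ratio to its own mean is 0.56 rather than 0.50. The loss is small at that point and matters mainly for the later years of objective 2.

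Third, this is a complementary analysis with no test attached, and the bias understates benefit, so it cannot create a false claim of effectiveness. That also stands and limits the severity.

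A reader might go further and infer that the effect disappears from objective 2, or that the hypothesis of no signals must fail by construction. The article does not support either. Full cancellation needs five post-release baseline years, which means post-year 6, or 2023 only for a zone whose last pre-effect year is 2017. The monthly threshold has no historical baseline and keeps the effect. A hypothesis of no signals becomes harder to sustain, but a fixed limit would not guarantee it either (0.07–0.09 per zone-year in the first simulated setting).

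A reader might also take the threshold section, which speaks of activity "in the post-intervention period, compared with pre-intervention, and we will report the number of months", to mean a before-and-after comparison only. Objective 2 already commits both indicators to treated versus untreated, so there is no contradiction.

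**Conclusion.** The concern holds for the control-diagram indicator alone. Followed as most naturally read, it attenuates a constant effect a little more each year. At RR 0.5, treated incidence relative to its own baseline mean moves from 0.50 to 0.83 over post-years 1 to 5. In the first simulated setting the treated/control ratio of weeks above the limit rises from 0.16 to 0.57, against 0.12–0.17 with a fixed window.

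The window counts and mean ratios rest on the moving-window reading, a constant RR and five retained baseline years. The simulated frequencies rest on assumed variability and change with the undefined epidemic-year rule, which may speed or slow the erosion. In every setting run, the moving-window ratio rose over follow-up and the fixed-window ratio showed no comparable rise. The primary interrupted time series is not affected. Severity: should be fixed, not critical.

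**What to change.** In the control-diagram section, and by reference in objective 2, state that for the evaluation:

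- Each zone's upper limit is computed from named pre-release years, the same calendar years for treated and control zones within a city, and held unchanged through follow-up. Because pilot releases began in late 2015, the years should be named explicitly.
- One stated rule identifies epidemic years and says whether they are replaced, applied identically to treated and control zones.
- Signals and outbreaks of two or more consecutive weeks are reported treated versus control against that fixed limit.
- The moving diagram is kept as a descriptive supplement.

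The cost is a few sentences and a small code change. No new data are needed, since the article says dengue notifications are available from 2000. The one drawback is that a fixed limit does not adapt to secular changes in reporting. Control-zone counts against limits built the same way address this.

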**2. Classical incidence threshold**

Another outbreak definition that has been used by the Ministry of Health (MoH) in previous years
^20,
22,
23^ is a dengue incidence threshold of ≥300 cases/100,000 population in a given month. Although not included in current MoH guidelines, this provides an alternative endpoint for evaluating dengue activity at a population level in the post-intervention period, compared with pre-intervention, and we will report the number of months in a given year where dengue incidence crosses this threshold.

### Current study status

This study is ongoing.
*Wolbachia* releases are expected to be completed by the end of 2019, and the collation and analysis of disease surveillance data will continue until 2023.

### Dissemination of study results

Based on the results of the power estimation above, the study outcome will be evaluated and reported two years after the completion of releases. The findings will be submitted for peer review and publication in an appropriate open access journal, together with aggregate supporting data.

## Discussion

The two cities of Rio de Janeiro and Niterói in southeastern Brazil have been affected by dengue for more than 30 years, with epidemics occurring every 2 to 5 years. In recent years, outbreaks of the other
*Aedes-*borne diseases chikungunya and Zika have presented further public health challenges. Vector control strategies, based on elimination of mosquito breeding sites and use of insecticides to reduce adult populations, have not been effective in preventing dengue outbreaks
^28^. The
*Wolbachia* method is a novel and self-sustaining approach for the biological control of arboviral diseases. The signature feature of
*Wolbachia* is to reduce the arbovirus-transmission potential of
*Wolbachia-*infected mosquitoes
^12,
14,
16,
17^. The World Mosquito Program
^29^ is deploying
*w*Mel
* Wolbachia*-infected
*Ae. aegypti* mosquitoes in Brazil with the purpose of achieving a large-scale and sustained reduction in arboviral disease burden in two cities where these diseases are public health priorities.

In March 2016, the WHO convened a Vector Control Advisory Group to review new and existing vector control tools for use in the response to the Zika virus outbreak. Based on the available evidence that
*Wolbachia* reduces the Zika, dengue and chikungunya transmission potential of
*Ae. aegypti* mosquitoes and field data showing long-term establishment of
*Wolbachia* in mosquito populations in a range of environmental settings, the WHO recommended carefully monitored pilot implementation of the
*Wolbachia* method in affected countries
^24^.

While RCTs are still considered the gold standard, they are not always feasible or agreeable to the community and government. The controlled ITS analysis is a quasi-experimental design that is commonly used to evaluate population-level public health intervention
^27,
30,
31^ and is a pragmatic alternative design where an RCT is considered infeasible, particularly in the presence of a well-matched untreated control area
^32,
33^. While the ITS approach could also be combined with randomization of the intervention, given the public health emergency posed by the Zika epidemic at the time of this study’s inception and the need to scale up
*Wolbachia* deployment in Rio de Janeiro and Niterói within a relative short time frame, randomized allocation of the
*Wolbachia* deployments was not considered feasible as it would have necessitated a fragmented approach to community engagement and release logistics which would have considerably complicated and delayed the implementation. The Brazil deployments were also an opportunity to optimise methods for large-scale deployment, and to evaluate the public health impact of a large contiguous release where the intervention area is likely to encompass a greater proportion of people’s daily movements, compared to a cluster randomised trial design. The controlled ITS is appropriate for the pragmatic evaluation of large-scale
*Wolbachia* deployments given the long and reliable time series of dengue mandatory reporting data from both Rio de Janeiro and Niterói that allows for a longitudinal assessment of dengue trends before and after the
*Wolbachia* intervention. Assessment of an impact of the intervention on chikungunya and Zika may be more difficult given their shorter time series.

Notifiable disease surveillance data can be limited by a lack of specificity in case definitions and inconsistent reporting practices, which may influence our ability to detect a true intervention effect on arboviral disease incidence. A subset of notified dengue cases are supported by laboratory diagnostic results, but these have several limitations: i) laboratory testing occurs infrequently (<15% of notified cases), particularly during outbreaks, ii) the cross-reactivity of IgM serology between dengue and Zika limits the utility of serological data since 2015, and iii) the restricted use of PCR in only certain patient populations limits the generalisability of PCR-positivity rates to all notified cases. We therefore base our analyses on all notified cases (suspected and confirmed). Benefits of using these routinely collected data include the availability of a long time series, reduced costs for data collection and timely acquisition of data. The non-randomized and unblinded nature of the
*Wolbachia* intervention means it is plausible that community awareness could alter health-care seeking behaviour, diagnostic or reporting practices in areas where
*Wolbachia* releases have been conducted. However we believe it is unlikely this would be of sufficient magnitude to result in a biased estimation of the intervention effect, since the intervention is deployed throughout such a large, diverse and complex setting (>120km
^2^, with population >1 million). We also cannot exclude the possibility of a concurrent change in socio-demographic or ecological factors related to dengue risk, or a change in dengue control practices, between the intervention and control areas independent of the
*Wolbachia* intervention, but given the strong synchrony in dengue incidence between intervention and control zones for over a decade prior to releases this is considered unlikely. 

Human mobility also presents a potential challenge to this study, especially during the period in which staged releases are occurring and
*Wolbachia* levels are heterogeneous, as individuals are likely to spend time in both
*Wolbachia*-treated and untreated areas, making it difficult to determine the place of illness acquisition among notified cases of arboviral disease. Travel between areas means that the true
*Wolbachia* exposure status of individuals resident in
*Wolbachia*-treated and untreated areas becomes more similar, thereby diluting the observed intervention effect towards the null.

The introduction of Zika and chikungunya viruses brought new challenges to health surveillance and a greater willingness for better vector control in affected regions. With the re-emergence of yellow fever in Brazil
^8^, there is even more potential public health benefit if the
*Wolbachia* intervention successfully reduces the vector competence of
*Ae. aegypti* mosquitoes in the field and reduces arboviral disease incidence. No specific treatment for dengue, chikungunya or Zika currently exists. Although a vaccine against dengue (Sanofi Dengvaxia
^®^) was licensed in 2015, it was recently found to enhance the severity of subsequent dengue infection in individuals who were seronegative at the time of vaccination. As a result, a serology test prior to the administration of the vaccine is required to confirm previous dengue infection, increasing costs and decreasing feasibility in high-burden areas
^34^.

Releases of
*Wolbachia* are completed or underway in eight countries, with no evidence of local transmission of dengue, Zika or chikungunya in places where
*Wolbachia* is established at high levels
^21^. The implementation of the
*Wolbachia* intervention is complex and has not been done on a large scale in very densely populated urban areas in the Americas before. The implementation of the project was preceded by careful work to engage the community and gain public acceptance for the intervention, even in the most difficult contexts of poverty and urban violence present in both Rio de Janeiro and Niterói. Engagement, entomological monitoring, and public health impact assessment activities were developed in close partnership with local governments. If the current project is successful, this model can be expanded to the rest of the country and the Americas.

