### Epidemiological data sources

The two proposed strategies for the evaluation of the impact of large-scale
*Wolbachia* deployments on arboviral disease incidence in Niterói and Rio de Janeiro make use of existing data on dengue, chikungunya and Zika case notifications to the Brazilian national disease surveillance system (SINAN). Dengue surveillance has been in place since its re-emergence in 1986 and data is available from the SINAN system since 2000. Zika and chikungunya became notifiable diseases in 2015.

Suspected cases of dengue and other arboviral diseases are required to be reported to the city health department
^25^, according to a case definition of fever plus two other symptoms including malaise, headache, myalgia, nausea, vomiting, cutaneous rash, and arthralgia. Dengue case notifications include an indication of disease severity (dengue, dengue with alarm signals, severe dengue, fatal dengue). A variable proportion of notified suspected cases are tested by IgM serology or PCR, following the Brazilian guidelines
^26^ and the timing between onset of symptoms and blood collection. The number of cases in a given period of time may limit the availability of tests, and PCR testing is routinely performed only for severe and fatal cases, pregnant women and young children
^26^. In 2016, 4.8% of notified dengue cases in Rio de Janeiro and 11.5% in Niterói were supported by a positive IgM serology result, and only 0.2% of notified cases in Rio and 0.03% in Niterói had a positive PCR result. The ability to confirm dengue cases by serology is impaired since the Zika outbreak due to serological cross-reactivity between the dengue and Zika viruses. As PCR testing is performed only in certain patient populations, the proportion positive is unlikely to be generalisable to all notified cases. Therefore, for the purpose of our analyses we will use all notified dengue cases (suspected and laboratory-confirmed) as the primary endpoint.

In the absence of a reliable serological test that does not cross-react with dengue, Zika lab diagnosis is done solely on the basis of molecular detection (real-time PCR) up to the first 5 days in serum and 15 days in urine. This has severely limited the ability to confirm Zika virus infection among notified cases (3.5% in 2016, 19.3% in 2017).

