Chikungunya diagnoses can be confirmed either through PCR or serology, as it does not cross-react with Zika or dengue. The proportion of notified cases with supportive laboratory findings is higher than for dengue: 31.9% and 18.2% in Rio and Niterói, respectively, in 2016.

Anonymized disaggregate (line-listed) data on notified suspected and laboratory-confirmed dengue, chikungunya and Zika cases will be extracted from the SINAN system for the historical pre-intervention period (2000–2016 for dengue, and 2015–2016 for chikungunya and Zika) and the prospective post-intervention period (2017–2023). The dataset will include age, sex, neighbourhood of primary residence, date of illness onset, date of notification, reporting health clinic, disease severity, hospitalisation, death, and where available, geocoordinates of primary residence, type of diagnostic test performed, diagnostic test result, and final diagnostic classification. Population data from the Brazilian census (IBGE) and population by neighbourhood of residence obtained from the cities of Rio and Niterói will be used to estimate the population in each release zone. The incidence rate (number of new dengue, Zika or chikungunya cases divided by the population at risk) will be expressed per 100,000 inhabitants.

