### Controlled interrupted time series analysis

Interrupted time series (ITS) analysis is a valuable study design for evaluating the effectiveness of a population-level health intervention that is implemented at a clearly defined point in time
^27^. It uses a set of historical observations of an outcome of interest (in this context monthly dengue case notifications) to establish an underlying trend, which is assumed to be ‘interrupted’ by the introduction of an intervention (in this case
*Wolbachia* releases). Comparison of the trend in monthly case notifications in the post-intervention period with the hypothetical scenario of no intervention (the ‘counterfactual’, inferred from the historical time series and the untreated control area), provides an estimate of the intervention effect. Segmented regression will be used to estimate the effect of
*Wolbachia* releases on monthly case counts of dengue and chikungunya, using an appropriately defined model: e.g. negative binomial regression for autocorrelated count data with population offset, adjusted for temporal effects using indicator variables or flexible cubic splines, and assuming a step change post-intervention. The
*Wolbachia* intervention effect will be estimated from the interaction between a binary ‘area’ variable (intervention vs control area) and a binary ‘period’ variable (post
*-*intervention
** vs
** pre
*-*intervention). The post-intervention period will be defined for the control area beginning at the same time as the post-intervention period in the comparative release zone. This allows explicitly for a level change in the outcome (dengue case incidence) in both intervention and control areas in the post-intervention period, for example in a scenario where other secular events coincident with the
*Wolbachia* deployments may have influenced dengue incidence in both intervention and control areas independent of
*Wolbachia*. An additional analysis will consider
*Wolbachia* frequency as a continuous covariate or categorised into quintiles of exposure reflecting the measured

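### The size of the setting does not make bias from differential notification unlikely; that risk, in either direction, needs stating and checking with the hospitalised cases

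*Protocol article*

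**What the plan says.** In the Discussion, the protocol article accepts that in a non-randomised, unblinded deployment "it is plausible that community awareness could alter health-care seeking behaviour, diagnostic or reporting practices in areas where" releases have taken place. It then concludes: "However we believe it is unlikely this would be of sufficient magnitude to result in a biased estimation of the intervention effect". The reason follows at once: "since the intervention is deployed throughout such a large, diverse and complex setting", with more than 120 km² and more than 1 million people given in support. No other reason is offered for this particular bias.

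Three other parts of the article bear on the point.

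- Epidemiological data sources: "we will use all notified dengue cases (suspected and laboratory-confirmed) as the primary endpoint". The line list is to include, among other items, "reporting health clinic, disease severity, hospitalisation, death, and where available, geocoordinates of primary residence", and test type and result where available.
- Controlled interrupted time series analysis: the "intervention effect will be estimated from the interaction between a binary ‘area’ variable (intervention vs control area) and a binary ‘period’ variable". Of defining the same post-intervention period for the control area, the article says: "This allows explicitly for a level change in the outcome (dengue case incidence) in both intervention and control areas in the post-intervention period".
- The same section lists severe and fatal dengue counts as secondary endpoints and plans an additional analysis by measured *Wolbachia* prevalence. Neither is presented as a check on differential notification. Hospitalisation, reporting clinic and test results have no stated role in such a check.

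**The concern.** A notified case requires a patient to attend and a clinician to suspect dengue and report it. Release areas received intensive community engagement before deployment, so any effect of awareness on these steps could run across the treated areas together and not appear in the control areas.

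The control area removes changes that both areas share. It cannot remove a change in notification confined to the treated areas, because the area-by-period interaction reads that change as part of the intervention effect. A large population narrows the interval around the estimate but does not move its centre. The argument in the Discussion therefore does not support its conclusion. At stake are the size of the reported effect and, for modest effects, whether one is declared at all.

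**Working it through.** **1. How the shift enters the estimate.** Let k be the post/pre change in the probability that a case is notified in the treated area, divided by the same change in the control area. The interaction then estimates

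observed RR = true RR × k.

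Population and area do not appear. The documents give no k, so the values below are assumptions.

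| k (assumed) | true RR 1.00 reads as | true RR 0.50 reads as |
|---|---|---|
| 0.8 | 0.80 | 0.40 |
| 0.9 | 0.90 | 0.45 |
| 1.1 | 1.10 | 0.55 |
| 1.2 | 1.20 | 0.60 |

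**2. Whether size or diversity helps.** Table 1 gives treated populations of 373,117 + 886,551 = 1,259,668 and treated areas of 83.2 + 85.5 = 168.7 km², so the article's description of scale is right. To see what scale does, the treated area was split into m subareas, each with its own notification shift (assumed median 0.8, log SD 0.2, true RR 1, 4,000 repeats).

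| m | mean observed RR | SD of log RR |
|---|---|---|
| 1 | 0.80 | 0.20 |
| 10 | 0.81 | 0.06 |
| 100 | 0.82 | 0.02 |
| 1000 | 0.82 | 0.006 |

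The spread disappears and the common shift stays. The small rise from 0.80 to 0.82 arises because the mean of a log-normal shift exceeds its median: 0.8 × exp(0.2²/2) = 0.816. Diversity would help only if local shifts ran in opposite directions and cancelled, which the article does not argue.

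**3. The plan's power figures, used to set a scale.** The article states 80% power for a 50% reduction after three years and for a 60% reduction after two. These cannot be reproduced exactly, because the fitted means, dispersion and autocorrelation are not given. With a two-sided 5% level assumed, the implied standard error of log RR is |ln RR| / (1.960 + 0.842):

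- three years, RR 0.5: 0.693 / 2.802 = 0.247
- two years, RR 0.4: 0.916 / 2.802 = 0.327

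As a plausibility check, take independent months, 84 before release, and variance 2φ(1/84 + 1/(12 × years)). Then φ = 0.77 gives 80% power at three years for RR 0.5, 89% at two years for RR 0.4, and 67% at two years for RR 0.5. The two power statements are therefore compatible on the coarse grid of effects simulated. They are not in dispute.

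**4. Chance of p < 0.05 when the true RR is 1.** By the normal approximation this is Φ(−1.96 − d) + Φ(−1.96 + d), with d = ln k / SE.

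| k (assumed) | SE 0.247 | SE 0.327 |
|---|---|---|
| 0.9 | 7% | 6% |
| 0.8 | 15% | 11% |
| 0.7 | 30% | 19% |
| 1.2 | 11% | 9% |

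For k = 1.2 the excess is almost all on the side of apparent harm. For k = 0.8, halving the SE of 0.247 raises the 15% to 44%. More precision makes a biased result more likely to be significant.

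**5. What would separate a reporting shift from an effect.** Suppose the shift affects mild cases only, hospitalised cases are a small part of all notifications, and severity mix changes alike in both areas. Treated-versus-control, post-versus-pre ratios would then be about:

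| Scenario | notified | hospitalised | hospitalised share |
|---|---|---|---|
| No effect, k = 0.8 | 0.80 | 1.00 | 1.25 |
| True RR 0.50, no shift | 0.50 | 0.50 | 1.00 |
| True RR 0.50, k = 0.8 | 0.40 | 0.50 | 1.25 |
| True RR 0.50, k = 1.2 | 0.60 | 0.50 | 0.83 |

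The share is the hospitalised ratio divided by the notified ratio. The patterns differ, so the check is informative.

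**The case against.** The limitation is disclosed, and several features soften it.

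- **Planned analyses already help.** Severe and fatal counts should depend less on care-seeking. An awareness effect need not follow measured *Wolbachia* prevalence, so the prevalence analysis and the zone-by-zone estimates carry some information. This stands in part. A reader might infer that nothing in the plan bears on this bias; that would be wrong. But severe and fatal counts may be sparse, and engagement and releases take place in the same zones, so the prevalence analysis separates the two only partly.
- **Sensitivity analyses may sit in an unseen analysis plan.** This also stands. Their absence from an article is weak evidence and does not carry the point. The size argument does, because the article states it and no further document would make it valid.
- **The magnitude is modest against the target.** A 10–20% shift under the null gives an RR of 0.90–0.80, not the 0.5 or 0.4 the study is powered for; producing 0.5 from nothing would need k = 0.5. Reporting is also mandatory, against a symptom-based definition. Both are better reasons for reassurance than scale, but the article does not use them here.
- **Laboratory results are a poor check.** The article explains why: under 15% of notified cases tested, IgM cross-reactivity with Zika, and PCR restricted to selected patients. This stands, and limits positivity to a supporting role.

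The Discussion's appeal to pre-release synchrony does not help. It is offered against other concurrent changes and cannot speak to behaviour that changes because of the releases.

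**Conclusion.** The point holds as a faulty argument in the text. The scale of the deployment gives no protection against a notification shift common to the treated areas, and such a shift passes in full into the primary estimate. Its size is unknown. With assumed k between 0.8 and 1.2, a true RR of 0.50 would be reported as 0.40 to 0.60. At k = 0.8 and no true effect, the chance of a significant result would be about 15% at three years instead of 5%. The latter figure rests on a normal approximation and on a standard error inferred from the stated power.

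A reader might go further and infer that the bias favours *Wolbachia*, or that a finding of the targeted size could be a reporting artefact. The documents support neither. They say only that behaviour could alter, with no direction; engagement could equally raise attendance or suspicion, which would understate the effect. A shift of 10–20% would not by itself produce a 50% reduction.

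**What to change.** 1. In the Discussion, delete the appeal to the size and diversity of the setting. State differential notification as a risk that could overstate or understate the effect.
2. Fit the same area-by-period model to counts of hospitalised notified dengue cases, and to the hospitalised share of notified cases (for example, with log notified cases as the offset in place of population).
3. Read these together with the planned severe and fatal endpoints, and name all of them as checks on differential notification. State the expected patterns beforehand: a fall in mild-case reporting alone should raise the hospitalised share and leave hospitalised counts unchanged, whereas a true effect should lower hospitalised counts as well.
4. Test positivity by area and period may be shown as supporting information only.
5. Treat any within-clinic comparison of treated-area and control-area residents as exploratory. It leaves patients' decisions to attend unaddressed, and probably draws on clinics near the boundary, where mixing dilutes the effect.
6. Use the checks to inform interpretation. Do not make attribution to *Wolbachia* conditional on passing them, since they are less precise than the primary analysis and have no agreed pass criterion.

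No new data collection is needed, because hospitalisation is already among the fields to be extracted. The cost is a few extra models with wider intervals than the primary analysis. The checks also assume that awareness does not alter admission itself.
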